**Methods:**

This study will be conducted in four HIV clinics in Ghana’s Central Region using a three-phase design.

Preparation Phase (Year 1): Use mixed methods, including nominal group techniques with 40–60 stakeholders (WLWH, healthcare providers, policymakers), to prioritize ISS and refine HOPE into HOPE 2.0 or HOPE-inG.

Implementation Phase (Years 2–3): Conduct a hybrid type 2 cluster-randomized controlled trial, comparing HOPE 2.0 + ISS (intervention group) versus HOPE 2.0 alone (control group). A total of 1,152 WLWH and 80 health providers will be enrolled.

Sustainment Phase (Years 3–5): Evaluate the long-term sustainment of HOPE 2.0 and ISS using quantitative and qualitative methods.

Primary outcomes include patient-level screening and treatment uptake (effectiveness) and provider-level implementation metrics (adoption, cost, fidelity, penetration and sustainability). Data sources include surveys, interviews, electronic tracking and fidelity checklists at multiple organizational levels. Cost analyses will employ micro-costing methods, and fidelity will be monitored through structured observations and log sheets.

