#### Sample size estimation

The sample size is calculated based on implementation outcomes of health system adoption, cost, fidelity, penetration, and sustainability.*For power calculation*, we used Power (1 − β) = 0.8 and α = 0.05 and did not assume equal cluster sizes. The coefficient of variation (CV) of cluster sizes is set to 0.2, allowing for a large variability between clusters. Methods from Donner et al. [59] implemented in R for cluster RCTs were used.*For binary outcomes**,* e.g., adoption, we assumed 15% adoption in the control group based on previous study [23]. Table 3 shows the sample size needed to detect increases in implementation outcomes (e.g., adoption) in the intervention arm from 15% to 25–50% with 80% power. We expect to achieve an increase of at least 15%, to 30% or more, for outcomes such as adoption.*For continuous outcomes* such as sustainability/sustainment, we used estimated variance = 1 (standardized), and variance within clusters = 0.95 (assuming a large proportion of individual WLWH variability). For average cluster sizes (sampling frame per facility) ranging from 400 to 600 WLWH, we have greater than 80% power to detect differences in mean scores between the intervention and control arms as small as 1.4. We aim to recruit at least 1,152 patients (288 per site × 4 sites, inclusive of 20% attrition for a minimum sample size of 240 per site) Thus, the sample size for the Intervention Arm is *n* = 576 and Control Arm is *n* = 576.

**Table 3 Tab3:** Power and sample size calculation

Intervention Numeric	Control Numeric	Minimum Sample Size Per Site
0.25	0.15	504
0.30	0.15	240
0.35	0.15	142
0.40	0.15	94
0.45	0.15	67
0.50	0.15	50

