### Outcomes measures

The primary outcomes of interest in this type 2 hybrid trial are 1) the effectiveness of the HOPE 2.0 intervention in increasing uptake of cervical screening among WLWH, and 2) the adoption of HOPE 2.0 intervention at the facility level. Other outcomes, including cost, fidelity, penetration, and sustainability, will be assessed as secondary outcomes. Additionally, Proctor et al.’s [61] client (i.e., WLWH) health outcomes will also be assessed (Fig. 2).*Cervical screening uptake* is defined as the proportion of WLWH in each study arm that successfully complete the cervical screening process. In the intervention arm, completing the process requires the WLWH to present to the clinic, collect a self-test kit, collect a cervical sample, and submit the sample to the clinic for testing. In the control arm, completing the process requires the WLWH to present to the clinic and receive a pap smear/cervical sample collection from a provider. WLWH in either study arm who do not complete the entire process will not be considered as completing uptake. Uptake assessment will therefore be determined as proportion of WLWH with complete screening out of all women enrolled in each study arm.*Program Adoption* is defined as the decision of healthcare workers (i.e., providers and management) and patients (described as patient uptake) to commit to and use HOPE 2.0 and ISS adoption. Adoption will be measured at provider, management, and patient levels using a variety of data logs, surveys, and interviews.At the management level, we will assess (i) the number of ISS training sessions attended and (ii) the degree to which ISS components are used to support providers.At the provider level, we will assess (i) the number of ISS training sessions attended, (ii) the degree to which ISS components are used, and (iii) the number of implementation plan steps followed. Additionally, we will assess providers’ (i) implementation experience (i.e., resource availability, managerial support, and technical issues confronted); and (ii) operational experience (i.e., workload increase or decrease, flow of health facility communication, and any skills needed).*Implementation Cost* is defined as the total expenses (facility/provider and patient) for implementing HOPE 2.0. Cost will be assessed at the health facility level in both study arms. We will use a micro-costing approach to estimate the economic costs associated with each study arm. The direct measure method of micro-costing involves tracking resources used and enumerating unit costs for each resource to precisely estimate cumulative costs associated with each study arm [62]. Implementation cost will be measured at the health facility level and patient level, utilizing a variety of cost-tracking databases throughout the study period to itemize, quantify, and value resources.At the health facility level, a cost-tracking database will be used throughout the study period to itemize, quantify, and value resources. Costs at the facility level include (i) number of hours staff spent on HOPE 2.0 training; (ii) sampling materials, including kits and laboratory testing costs; (iii) recruitment (i.e., time spent identifying and contacting eligible women, advertising materials, participant incentives); (iv) HOPE 2.0 delivery (with and without ISS); and (v) treatment and biopsies.Cost to the patient will include tracking of participant out-of-pocket costs (e.g., transportation, childcare, phone data, time spent on HOPE 2.0 procedures). French et al.’s outpatient cost survey [63] (5 items) will be adapted to measure patient-level costs.Note: Time effort will be estimated using the hourly wages of WLWH and healthcare workers.*Fidelity* is the degree to which HOPE 2.0 and its ISS are implemented as planned.At the provider level, utilizing surveys, log sheets, and interviews, we will assess (i) the degree of adherence to HOPE 2.0/ISS protocols (Intervention) and HOPE 2.0 (Control) during implementation, (ii) the dose of the program delivered, and (iii) the quality of program delivery.At the management level, we will assess (i) adherence to ISS protocol (Intervention only) and (ii) overall management support for providers (both arms).We will utilize log sheets and interviews, as well as observations, and the Process Evaluation Checklist (PEC) [64] throughout to track the fidelity of implementation and overall project progress.*Program Penetration* for this proposal is the integration of HOPE 2.0/ISS within the HIV subsystem of study facility settings [61]. We will assess penetration outcomes at provider and management levels by determining the proportion of personnel who actually deliver on a HOPE 2.0 program task/role, out of the number trained or expected to deliver on that task/role.At the management level, we will utilize log sheets and interviews to measure the expected tasks or roles to be evaluated, which will be (i) the provision of technical support and (ii) facilitating a conducive HOPE 2.0 implementation climate for providers.At the provider level, we will utilize log sheets and interviews to measure the expected tasks to be evaluated, which are (i) screening and recruitment of eligible WLWH, (ii) delivery of HOPE 2.0 to enrolled WLWH, and (iii) follow-up on all testing outcomes and completion of required documentation for these tasks/roles.*Program Effectiveness* is defined as the impact of the ISS on 1) providers' self-efficacy in implementing HOPE 2.0, 2) WLWH screening uptake, and 3) treatment outcome. We will assess effectiveness outcomes at management, provider, and WLWH levels utilizing surveys, log sheets, and interviews.At the management level, we will assess (i) the frequency of support that management delivers to providers, (ii) management self-efficacy in supporting HOPE 2.0 implementation, and (iii) challenges in supporting HOPE 2.0 implementation at their facilities, utilizing log sheets and interviews.At the provider level, we will assess (i) self-efficacy for implementing HOPE, (ii) fidelity of HOPE 2.0 intervention delivery, (iii) number of WLWH screened and women with positive results who are treated, and (iv) the type, frequency, duration, and quality of service provided to patients (WLWH).At the WLWH level, we will assess the impact of HOPE 2.0 on patients’ (WLWH) screening uptake (i.e., service outcome) and receipt of screening results, patient satisfaction, and for women with positive screening results, clinical follow-up, and evaluation for, and receipt of CC treatment where appropriate (i.e., client outcomes). Assessment procedures: WLWH in both study arms will complete the screening and satisfaction outcome survey within one month of completing HOPE 2.0. Within one month of screening, providers will check the lab registry and will review the electronic medical record to confirm screening completion. Treatment compliance will be evaluated within 6 months of positive result notification. The screening and treatment completion outcomes will be binary (yes/no), test results (positive, negative, or inadequate), treatment follow-up (yes, no, or lost-to-follow-up), and patient satisfaction will be measured using a patient satisfaction survey [65].

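### Adoption, the second primary outcome, is stated at facility level but defined to include patient uptake, which is the first primary outcome, so the implementation and effectiveness conclusions are not clearly separate

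*Protocol article*

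**What the plan says.** The Outcomes measures section of the protocol article names two primary outcomes. The first is "the effectiveness of the HOPE 2.0 intervention in increasing uptake of cervical screening among WLWH"; the second is "the adoption of HOPE 2.0 intervention at the facility level".

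Uptake is then given a numerator and denominator: "Uptake assessment will therefore be determined as proportion of WLWH with complete screening out of all women enrolled in each study arm".

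Adoption is defined in the next entry as "the decision of healthcare workers (i.e., providers and management) and patients (described as patient uptake) to commit to and use HOPE 2.0", and the sentence goes on to include adoption of the ISS. The section adds: "Adoption will be measured at provider, management, and patient levels using a variety of data logs, surveys, and interviews". The items then listed cover managers and providers only:

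- ISS training sessions attended (both groups)
- the degree to which ISS components are used (both groups)
- implementation plan steps followed (providers)
- implementation and operational experience (providers)

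The abstract groups adoption with "provider-level implementation metrics (adoption, cost, fidelity, penetration and sustainability". The hypothesis under Implementation phase likewise contrasts screening uptake among the women with implementation outcome scores among providers.

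Under Sample size estimation, adoption is the example of a binary outcome: "we assumed 15% adoption in the control group based on previous study", and "We expect to achieve an increase of at least 15%, to 30% or more, for outcomes such as adoption". The result is 240 women per site, raised to 288 for attrition, or 1,152 over four sites.

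**The concern.** A type 2 hybrid trial is meant to answer two questions: whether women are screened more, and whether the health service takes the programme on. Making uptake and adoption separate primary outcomes serves that purpose only if they measure different things.

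Here the level of the second primary changes with the sentence. It is the facility in the list of primaries, three levels including patients in the definition, providers in the abstract and the hypothesis, and in effect women in the sample size. The patient level is given the name of the first primary outcome. If it contributes to the adoption result, screening events support both conclusions, and any bias in measuring uptake passes into the adoption result. A reader of the final report could not tell whether a positive adoption finding says anything about staff beyond what uptake already showed.

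**Working it through.** **1. The level of adoption, side by side.**

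| Place in the protocol article | Level of adoption |
|---|---|
| Abstract, Methods | provider |
| Implementation phase, hypothesis | provider (implementation outcome scores) |
| Outcomes measures, list of primaries | facility |
| Outcomes measures, definition | provider, management and patient |
| Outcomes measures, itemised measures | management and provider |
| Sample size estimation | a proportion, used to size a sample of women |

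No sentence says how the levels combine or which one carries the primary conclusion.

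**2. Which adoption measures can differ between arms for a reason other than allocation?** Table 2 marks the implementation plan and ISS topics (rows 9 to 12) as not given in the control arm. The Control arm section says that control sites receive no ISS or implementation plan training. ISS materials reach them only after the 6-month comparison. ISS sessions attended, ISS components used and plan steps followed are therefore zero or undefined in control by design. The experience items can be collected in both arms, but they describe resources, support and workload and do not measure whether the programme was taken up. Of the named components, that leaves patient uptake.

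**3. What the 15% can refer to.** A 15% control rate cannot describe use of ISS at sites that receive none. The document's own arithmetic also counts women: 240 × 1.2 = 288 per site, and 288 × 4 = 1,152 women.

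The 240 cannot be reproduced from stated inputs, because no intracluster correlation (ICC) is given for binary outcomes. With an assumed value:

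- Without clustering, n per arm = (1.960 + 0.842)² × (0.30 × 0.70 + 0.15 × 0.85) / 0.15² = 117.7.
- Taking the stated coefficient of variation of 0.2, a cluster size of 500 (midpoint of the stated frame of 400 to 600 women) and an assumed ICC of 0.002, the design effect is 1 + (1.04 × 500 − 1) × 0.002 = 2.038.
- The product is 239.9, against the stated 240. The other five rows of Table 3 come out at 503.9, 142.0, 94.1, 66.7 and 49.3, against 504, 142, 94, 67 and 50.
- At the same ICC, cluster sizes of 400 and 600 give 215.5 and 264.4.

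The match depends on the assumed ICC and proves nothing alone. It is consistent with a calculation built on clusters of women. (On this assumption the figures are per arm although the table says per site, which is a separate matter.)

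**4. What staff-level adoption would rest on.** The abstract gives 80 providers. Split evenly, which is an assumption, that is 40 per arm. Even with no clustering, 15% against 30% needs about 118 per arm. With 40, the standard error is √((0.21 + 0.1275)/40) = 0.0919, z = 0.15/0.0919 = 1.63, and power is Φ(1.63 − 1.96) ≈ 0.37. Clustering in four sites lowers it further.

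**5. Does the overlap inflate type I error?** With each primary tested at 0.05, the chance of at least one false positive is 1 − 0.95² = 9.75% if the tests are independent, 7.8% at a correlation of 0.8 and 5.0% if they are identical. Overlap lowers this figure.

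**The case against.** The strongest defence is that the separation was intended and is visible. The abstract and the hypothesis put uptake with women and implementation outcomes with providers, and the itemised adoption measures contain no patient item. The parenthesis about patient uptake can then be read as a cross-reference: at patient level the concept is reported under the other heading, and nothing is counted twice. This reading is possible, and it shows what the authors probably meant. It does not remove the conflict, because the next sentence says adoption will be measured at patient level, and it leaves no staff measure that can be compared between arms.

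A reader might infer more: that adoption can be declared on uptake data alone, or that the two outcomes are perfectly correlated, so that success on one guarantees success on the other. The document does not support this. It gives no composite and no any-component rule, and adoption also has management and provider parts and extends to the ISS. Uptake in the control arm is defined through a smear or a sample taken by a provider, which is not plainly use of HOPE 2.0, so the events may differ in that arm. (That definition also sits badly with the Control arm section, which has control sites follow the self-sampling steps; the two need reconciling.)

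It is also fair that adoption is only an example in the sample size section, and that sizing women on it is a problem of unit. It remains evidence of how adoption was understood when the trial was sized.

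Analysis detail may lie in a plan not shown. The level and unit of a primary outcome are stated here, however, and stated inconsistently.

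**Conclusion.** The point holds as a contradiction in the definition of a primary outcome. Adoption is assigned to different levels in different places, and its patient part bears the name of the first primary. As written, a between-arm adoption result would either follow from which sites were given ISS and the plan, or fall back on uptake. The implementation conclusion is therefore not clearly separate from the effectiveness conclusion.

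The amount of overlap cannot be quantified from the text, and the overlap does not raise the type I error rate. The conclusion rests on reading the definition literally and on control sites having no ISS or plan during the comparison, which the document states. It does not depend on the assumed ICC. The change should be made before outcome data are analysed; it does not call the design itself into question.

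**What to change.** 1. Remove patients and patient uptake from the adoption definition, and report uptake only under the first primary outcome.
2. Name one staff-level adoption measure with its unit and denominator. It must be able to take values in both arms and must differ from Program Penetration, which is already the share of personnel who deliver a task. One example is the proportion of HOPE 2.0 delivery steps common to both arms that each provider uses, summarised by site. Measures of ISS and plan use can stay as descriptive results for the intervention arm.
3. Use the same level in the abstract, the list of primaries and the definition.
4. Relabel the 15% to 30% scenario under Sample size estimation as screening uptake. State that adoption rests on about 80 providers at four sites and that the calculation for 1,152 women does not power it.

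The edits are a few sentences. The log sheets and surveys already planned for providers may suffice, provided they record each common step in both arms. The real cost is that adoption loses its stated 80% power. Because control providers are also required to follow the common steps, the example measure may separate the arms poorly, so the sponsor should consider that before fixing it.

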### Implementation phase

Assess the effectiveness of the HOPE 2.0 intervention and the success of the implementation plan in a hybrid type 2 trial.

*Hypothesis: Cervical screening uptake by HPVSS will be significantly higher among WLWH in the intervention vs. the control group, and implementation outcomes scores among intervention group providers will be significantly higher than those of control group providers.*

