#### Control arm

Providers and clinic managers at control sites will receive baseline training on study implementation, but will not receive any ISS or implementation plan training (Table 2). They will, however, be required to follow Steps 2, 3, and 4 described in the intervention arm described above, except for patient navigator support.

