#### Quantitative data analysis

Descriptive analysis will be used for implementation outcomes scores at each health facility; scores will be compared within health facilities and between study arms over time. Mixed models (Linear Mixed Models or Generalized Linear Mixed Models) will account for repeated participant measures.*For Likert scale items (surveys)*, we will use ANOVA to determine differences in implementation outcome scores between study arms, with Tukey HSD (honestly significant difference) post hoc analysis to determine specific sites that significantly differ.*For continuous outcome variables*, we will similarly use linear mixed models to analyze treatment effects while controlling covariates, including age, education, income, religion, marital status, employment, insurance, and clinical conditions consistent with our previous studies [68, 69].*Fidelity analysis:* The fidelity checklist and activity log sheets at each study site will be aggregated, and composite site scores will be calculated and compared across intervention and control sites.*Cost-Effectiveness Analysis:* Costs will be determined using the cost trackers described. At the facility level, we will use the WHO Incremental Cost-Effectiveness Ratio (ICER) [70]. A formula to analyze the cost-effectiveness outcome, whose outcome of interest is screening and treatment. An ICER is calculated by dividing the difference in total costs (incremental cost) by the difference in the chosen measure of health outcome or effect (incremental effect) to provide a ratio of ‘extra cost per extra unit of health effect. We will determine the Total Cost [average fixed and variable costs (TC)] for screening and treatment in IG (Arm 1) and CG (Arm 2), and cervical cancer cases averted (incremental effect) for each Arm. Then ICER = Incremental cost/Incremental effect. An ICER of less than 1 indicates that the control group is cost-effective, an ICER greater than 1 suggests the intervention group is cost-effective, and an ICER equal to 1 indicates a similar cost for both arms. At the patient level, we will calculate the average cost per patient in both arms.

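### The staff-level measures of the co-primary outcome, adoption, count support strategies and plan steps that control sites are not given, so they cannot compare use of HOPE 2.0 between arms

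*Protocol article*

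**What the plan says.** Under Outcomes measures, the article names two primary outcomes: screening uptake and "2) the adoption of HOPE 2.0 intervention at the facility level". It defines adoption as the decision of staff and patients "to commit to and use HOPE 2.0 and ISS adoption", and then lists what will be measured.

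- Managers: "i) the number of ISS training sessions attended and (ii) the degree to which ISS components are used to support providers".
- Providers: ISS sessions attended, then "ii) the degree to which ISS components are used, and (iii) the number of implementation plan steps followed". Providers' implementation experience (resources, managerial support, technical problems) and operational experience (workload, communication, skills) are assessed in addition.
- Patients: adoption is equated with patient uptake.

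The Control arm section says that control providers and managers "will not receive any ISS or implementation plan training". Table 2 agrees: topics 9 to 12 (implementation research, the plan, ISS, additional tools and job aids) are given to the intervention arm only. The Design section of the Implementation phase says that control sites get ISS materials only once the six-month implementation period is over.

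The hypothesis is that "implementation outcomes scores among intervention group providers will be significantly higher than those of control group providers". Quantitative data analysis plans comparisons of implementation outcome scores between arms. For fidelity, "composite site scores will be calculated and compared across intervention and control sites".

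**The concern.** A between-arm outcome has to be something that either arm could achieve. The trial asks whether adding ISS and a plan makes clinics use HOPE 2.0 more. If use is measured by ISS sessions attended, ISS components applied and plan steps followed, the measure records whether the site was given ISS. The intervention arm then scores higher even where staff in both arms deliver HOPE 2.0 equally well, and the hypothesis on provider scores could be declared confirmed for that reason. This touches a co-primary outcome, not a descriptive process measure.

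**Working it through.** **1. Each listed staff measure against what control sites receive in the first six months**

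| Level | Measure | Available to control? |
|---|---|---|
| Manager | ISS sessions attended | No; zero short of contamination |
| Manager | ISS components used | No; zero short of contamination |
| Provider | ISS sessions attended | No; zero short of contamination |
| Provider | ISS components used | No; zero short of contamination |
| Provider | Plan steps followed | No plan given; may exceed zero where plan steps coincide with Steps 2 to 4 |

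Count: 2 manager + 3 provider = 5 measures, of which 4 are ISS items and 1 is a plan item. None measures use of HOPE 2.0 as such.

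**2. Whether the rest of adoption fills the gap**

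Patient-level adoption can be measured in both arms, but it is uptake, which is already the first primary outcome. Provider implementation and operational experience can also be collected in both arms, but they describe what delivery was like, not whether or how much HOPE 2.0 was delivered. No listed adoption measure is at once distinct from uptake, comparable between arms, and a measure of HOPE 2.0 use by staff.

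**3. Whether the article confines the ISS items to one arm**

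For fidelity it does: management adherence to the ISS protocol is marked as applying to the intervention arm only, and overall management support as applying to both. Adoption carries no such marking.

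**4. Direction and possible size**

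Suppose a staff score gives weight w to ISS items and 1 − w to HOPE 2.0 use. Let HOPE 2.0 use be h in both arms (no true effect), and ISS use be q in the intervention arm and 0 in control.

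Difference = [wq + (1 − w)h] − [w·0 + (1 − w)h] = wq.

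Both w and q are assumptions; the article gives neither.

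| q | w = 1/3 | w = 1/2 | w = 1 |
|---|---|---|---|
| 0.30 | 0.10 | 0.15 | 0.30 |
| 0.50 | 0.17 | 0.25 | 0.50 |

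The difference is positive for any w and q above zero, and it vanishes only at w = 0, when ISS items are left out.

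**5. What the 15% control rate in Sample size estimation refers to**

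Table 3 gives 240 per site for 15% versus 30%. With unpooled variance:

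n per arm = (1.960 + 0.842)² × (0.30×0.70 + 0.15×0.85) / 0.15² = 7.849 × 0.3375 / 0.0225 = 117.7.

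The stated coefficient of variation is 0.2. The stated within-cluster variance of 0.95 out of 1, given for continuous outcomes, implies an intraclass correlation of 0.05. With an assumed mean cluster size of 60, which the article does not state:

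Design effect = 1 + (1.04×60 − 1)×0.05 = 4.07.

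Then 117.7 × 4.07 / 2 sites = 239.6, or 240. The other five rows of Table 3 reproduce in the same way, though other pairs of cluster size and correlation give the same design effect. The article then takes 240 × 1.2 = 288 patients per site, and 288 × 4 = 1,152.

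The Abstract plans 80 providers, or 20 per site on average, so 240 per site can only be women. The 15% therefore reads as patient-level adoption and has no bearing on the staff items.

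**The case against.** A reader might infer that the intervention arm wins by allocation alone and that the second primary outcome carries no information. The article does not support that, for these reasons.

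- Adoption is measured at three levels. The patient level and the two provider-experience measures do not depend on ISS.
- It is not established that all five staff items are zero in control. The Control arm section requires Steps 2, 3 and 4 apart from navigator support, so plan steps followed may exceed zero.
- Recording ISS use at control sites has a purpose. Anticipated challenges and mitigation strategies foresees contamination and a complier average causal effect analysis, which needs such a record.
- The article gives no rule for combining the items. It may leave that to the full protocol, and its absence is no fault here. Any fixed percentage for the artefact would be invented.
- The 15% control rate is not contradicted by the staff items, because it sizes the sample of women.
- Fidelity does not share the flaw. Provider fidelity is scored against each arm's own protocol, so control is not zero by design. Penetration is also defined on tasks that control staff perform.

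All of this stands, and it limits the claim. It does not remove it: the listed staff measures of a co-primary outcome are still not comparable between arms, and nothing in the text restricts them to one.

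**Conclusion.** The point holds for the staff-level part of adoption and should be corrected before outcomes are analysed. Four of the five listed measures are zero in control short of contamination; the fifth is not comparable. The direction of the artefact is fixed, in favour of the intervention arm. Its size is unknown: under the assumed weights and use rates above it runs from 0.10 to 0.50 with no difference in HOPE 2.0 use. The conclusion rests on control sites receiving neither ISS nor the plan for six months, as the article states, and on the listed measures entering the between-arm comparison, as the hypothesis and analysis sections imply.

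Two lesser points go with it. The fidelity composites differ in content between arms (HOPE 2.0 with ISS against HOPE 2.0 alone) but are to be compared. The Abstract also lists "provider-level implementation metrics (adoption, cost, fidelity, penetration and sustainability" among the primary outcomes, whereas Outcomes measures makes all of these except adoption secondary.

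**What to change.** - Define between-arm staff-level adoption only on HOPE 2.0 actions expected of both arms: recruiting women, sending 3R messages, giving out kits and documenting follow-up, without navigator support.
- Preferably express it as degree of use: the share of eligible or enrolled women for whom each step was delivered. A rule that a provider counts once a step is delivered to at least one woman would nearly repeat penetration. It would also risk a ceiling, since 1,152 women over 80 providers is about 14 each and control staff are required to perform these steps.
- Report ISS and plan items as process measures for the intervention arm, and in control only to detect contamination.
- State that the 15% control rate refers to patient-level adoption.
- Compare fidelity composites between arms only on HOPE 2.0 items common to both.
- Make the Abstract's list of primary outcomes agree with Outcomes measures.

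One dependency: the kit item is common to both arms according to the Control arm section, but the uptake definition describes provider-collected samples in control. Those two passages must be reconciled first.

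The cost is outcome wording. Log sheets for recruitment, delivery and follow-up are already planned under penetration. The article does not say whether they are kept per woman; if not, that field must be added. The Discussion places the trial at the start of the Implementation Phase, so the change can still precede outcome analysis.
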